### Power analysis determining number of participants.

We will analyze *MGMT* promoter methylation in WBC samples collected at study inclusion from incident cases of colon cancer, glioblastomas and high-grade diffuse B-cell lymphomas and in matched controls drawn from the WHI biobank in a nested case-control design. With respect to **statistical power**, in preliminary analyses, measuring *MGMT* WBC methylation in umbilical cord blood from girls in the Norwegian Mother and child study (MoBa), we found WBC *MGMT* methylation in 197/1260: 15.6% of newborn girls (95% CI: 13.7 -17.8%). From mothers (age 20-40), *MGMT* methylation was revealed among 100/575; 17.3.% (CI: 14.4-20.7%).

While some evidence indicates that *MGMT* methylation may occur more frequently in right- as compared to left-sided colon cancers (101), this is not firmly established. On the other hand, there is no evidence indicating *MGMT* methylation may occur at a higher frequency in left-sided colon cancer or rectal tumours as compared to right-sided / transversal cancers. Taking into account the biological differences between right- versus left-sided colon cancers, for this study, we will analyse *MGMT* methylation status in right-sided and left-sided colon cancers separately.

We will use our preliminary data for methylation / SNP rs16906252, obtained from young adults, as basis for estimates of statistical power. A modest correlation between the rs16906252 and promoter methylation has been reported previously (86, 87, 89, 92, 102). In our data set, among 575 individuals, 35 were methylated carrying the variant allele (6.1%), 49 carried the variant allele without *MGMT* methylation (8.5%), 65/575 were homozygous for the reference rs16906252 allele carrying *MGMT* methylation (11.3%), while 426/575 (74%) were homozygous for the reference allele and did not carry *MGMT* methylation.

The figures above allow testing potential effects of the SNP allele and *MGMT* methylation separately on colon cancer risk. For both tests, we assume a HR of at least 2.

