**Testing for the effect of *MGMT* methylation status among individuals not carrying the SNP variant.** Removing all carriers of the SNP rs16906252 variant allele (among young women 84/575; 14.6%), less than 20% of participant in total will be omitted from the statistical analysis. In the group homozygous for the reference rs16906252 allele 65/491 carry *MGMT* methylation (13.2%). For a 1 : 2 matched nested case control design assuming a HR of 2 and

assuming a methylation frequency of 12% we will need 195 cancer patients (Table 1). Assuming a methylation frequency of 8%, this number increases to 310. Assuming up to 20% of all individuals to be either homo- or heterozygous for the variant allele, another 66 patients need to be added. Accounting for some samples being lost to analytical failure, starting with  $n = 400$  patients with 800 controls in a 1 : 2 design will provide an adequate sample size.

**Testing for the effect of *MGMT* variant allele status among individuals not carrying *MGMT* promoter methylation.** Out of 575 individuals, in total 100 were found methylated at the *MGMT* promoter (17.4%). Among the non-methylated individuals (82.6%; 475/575), 10.3%; (49/475) had the variant allele. Assuming the variant allele to be found among 8% (or more) of individuals, the calculations above will apply, confirming a total of  $n = 400$  patients and 800 controls will be adequate for this test as well.

Taken together, we are able to test for the effect of *MGMT* methylation and the variant rs16906252 allele separately in nested case-control cohorts of 400 patients and 800 controls in a robust design. Thus, we aim testing for potential impact of *MGMT* methylation status and the rs16906252 variant allele on HR for right- and left-sided colon cancer (2 separate cohorts) with 400 patients and 800 matched controls for each comparison.

The fact that glioblastoma is a less common cancer form does not exclude constitutional *MGMT* methylation as a potential risk factor. As for glioblastomas, in the WHI study a total of  $n = 195$  glioblastomas are so far recorded. Assuming a methylation frequency in the normal population of between 12 and 15% and a cancer OR of 2, a potential impact of *MGMT* promoter methylation may be tested in the total group with a power of 0.9 (Table 1), and the impact of *MGMT* methylation and rs16906252 variant allele status separately with a power between 0.8 and 0.9, assuming a 1 : 4 nested control design.

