Considering diffuse large cell B-lymphomas, the WHI contains more than 500 cases. With the *MGMT* methylation frequencies recorded in the literature, we assume a HR and statistical power calculation resembling that performed for each of the two colon cancer groups. Thus, we will enroll  $n = 400$  lymphoma cases with 800 matched controls.

**Table 1.** Overview of sample sizes required given  $\alpha = 0.05$ ,  $1-\beta = 0.8$  or  $0.9$ , and OR in the range of 1.3 – 3.0, for different percentages of methylated healthy individuals (controls) in the population. The numbers listed are given as the number of cancer cases required, given a 1:2 matched design (2 healthy controls per analyzed cancer case) or a 1:4 matched design

| HR  | Power ( $1-\beta$ ) | Match 1 : 2 |      |      | Match 1 : 4 |      |      |
|-----|---------------------|-------------|------|------|-------------|------|------|
|     |                     | 8 %         | 12 % | 15 % | 8 %         | 12 % | 15 % |
| 1.5 | 0.8                 | 780         | 490  | 375  | 604         | 378  | 290  |
| 1.5 | 0.9                 | na          | 650  | 500  | 783         | 483  | 377  |
| 2.0 | 0.8                 | 230         | 145  | 112  | 186         | 115  | 87   |
| 2.0 | 0.9                 | 310         | 195  | 150  | 236         | 147  | 111  |
| 3.0 | 0.8                 | 75          | 47   | 35   | 62          | na   | na   |
| 3.0 | 0.9                 | 100         | 62   | 45   | 77          | na   | na   |

**Summary of individuals to be enrolled.** Based on the estimates above, for the colon cancer study we need to enroll a total of  $n = 800$  participants with colon cancers and a total of  $n = 1.600$  controls. For the glioblastoma study, we will enroll all 195 participants developing glioblastomas with  $n = 780$  controls, while for the lymphoma study 400 cases and 800 controls will be included. **This adds to a total number of 4.575 individuals.** However, like for the previous *BRC1* study, we assume several control individuals may act as controls in different comparisons; thus, most likely this number of control individuals may be reduced. In our previous study on breast- and ovarian cancers (WHI AS543), we were able to reduce the total number of controls by about 23% by using some of the same controls for both comparisons. As

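### The allowance of 66 cases for excluded SNP carriers should be 78; 400 cases still cover it, but with half the implied margin and only if the variant itself carries no risk

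*Protocol*

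**What the plan says.** The size of each colon cancer cohort is derived in the protocol, section 'Power analysis determining number of participants', in the paragraph on methylation among women who do not carry the SNP variant.

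- The effect size serves both the methylation test and the variant test: "For both tests, we assume a HR of at least 2".
- At 12% methylation, 195 cases are required. For a lower prevalence: "Assuming a methylation frequency of 8%, this number increases to 310". Both numbers are the Table 1 entries for HR 2.0, power 0.9 and 1:2 matching. The paragraph does not name the power.
- For the carriers who will be left out: "Assuming up to 20% of all individuals to be either homo- or heterozygous for the variant allele, another 66 patients need to be added". This makes 310 + 66 = 376.
- The total is then raised to 400 cases and 800 controls to cover analytical failures. No failure rate is given.

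The observed carrier share is 84/575 (14.6%), and the observed methylation prevalence among non-carriers is 65/491 (13.2%). The same 400/800 is carried over to the variant test, to both colon cohorts and to the lymphoma cohort.

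**The concern.** Two things look wrong.

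First, 66 does not follow from 310 and 20%. An allowance for exclusions should be found by dividing by the retained fraction, and the stated figure is too small for that.

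Second, the carrier share is that of the general population, but the required number is a number of cases. The protocol plans to test the variant as a risk factor with an assumed HR of at least 2. If that holds, carriers are over-represented among cases, and more than 20% of cases are lost to the exclusion.

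This is the only derivation of the 400/800 size, so an error here reaches every cohort that reuses it. At stake is whether the power behind the 310 survives the exclusion, and how many failed samples the design can bear.

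**Working it through.** **Inputs (all from the protocol's power section).** Required analysable cases at 8%, HR 2, 1:2: 310 (power 0.9) and 230 (power 0.8). At 12%: 195 (power 0.9). Carrier share: 20% (planning ceiling) or 14.6% (observed). Variant HR: 2. Enrolment: 400 cases, 800 controls.

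**1. Trying to reproduce the 66.**

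| Carrier share | n/(1 − d) − n | n × d |
|---|---|---|
| 20% | 310/0.80 − 310 = 77.5, so 78 | 62 |
| 14.6% | 310/0.854 − 310 = 53 | 45.3, so 46 |

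No stated input gives 66. It would take a loss of about 17.5% (310/0.825 = 376), which the text does not mention. The correct total is 388. With 376 cases, 376 × 0.80 = 301 remain, 9 short of 310.

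**2. What 400 leaves.** 400 × 0.80 = 320, which is at least 310. Room for failures: 400 − 388 = 12 cases (3%), against the implied 400 − 376 = 24 (6%). The exact break-even is 1 − 310/320 = 3.1% failure. At 5% failure 304 cases remain; at 10%, 288.

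**3. Power on Table 1's own scale.** To avoid bringing in another formula, I interpolate between the table's two entries at 8%. The normal quantile of power is taken as linear in √n:

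z(n) = 0.8416 + (1.2816 − 0.8416)/(√310 − √230) × (√n − √230) = 0.8416 + 0.1802 × (√n − 15.166)

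| Analysable cases | Situation | z | Power |
|---|---|---|---|
| 320 | 20% carriers in cases, no failures | 1.332 | 0.909 |
| 310 | 3.1% failures | 1.282 | 0.900 |
| 304 | 5% failures | 1.251 | 0.894 |
| 288 | 10% failures | 1.167 | 0.878 |

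**4. Carrier share among cases if the variant has HR 2.** With share q in controls, the share in cases is 2q/(1 + q), taking the HR of 2 to apply to carriers as a whole.

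- q = 0.146: 0.292/1.146 = 25.5%, leaving 400 × 0.745 = 298 cases; z = 1.220, power 0.889.
- q = 0.20: 0.40/1.20 = 33.3%, leaving 400 × 0.667 = 267 cases; z = 1.053, power 0.854.

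These figures keep two controls per retained case, as the table's caption defines it: "given a 1:2 matched design (2 healthy controls per analyzed cancer case) or a 1:4 matched design". If all non-carrier controls are kept instead (683 or 640), the ratio rises to about 2.3 or 2.4. Scaling the case number by 1.5/(1 + 1/ratio) gives an equivalent 311 or 283 cases at 1:2, and power of about 0.90 or 0.87. The spare controls therefore recover one to two points.

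**5. At 12% methylation.** Table 1 requires 195 cases for 0.9. Even 267 exceeds this, so power stays above 0.9 with or without a variant effect. The same is true at the observed 13.2%.

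**The case against.** The strongest reply is that nothing depends on the 66. The enrolled number is 400, which leaves 320 cases after a 20% exclusion and so meets the table's 310. This stands. A reader might infer from the wrong allowance that 400 fails to reach 0.9 at 8% outright. The protocol's figures do not support that: 0.9 is lost only if more than about 3% of samples fail, or if the variant raises risk. An unmatched two-proportion formula (odds ratio 2) does give 0.89 at 320/640, but it gives only 0.88 at the protocol's own 310/620. That gap comes from the choice of formula, not from the allowance.

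It is also fair to say that the low end, 0.85, combines cautious choices: a 20% carrier ceiling against 14.6% observed, 8% methylation against 13.2% observed, and a full HR of 2 for the variant. That is why a range is given. The HR of 2 is nevertheless the protocol's own assumption, and 14.6% carriers in controls is already enough to bring the cases below 310.

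A reader might also infer that dropping a carrier breaks its matched set, so that the statement "less than 20% of participant in total will be omitted from the statistical analysis" is wrong. The section on statistical analysis names Cox and logistic regression with covariates and does not require whole sets to be discarded. The sentence counts carriers, observed at 14.6%, and can stand.

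**Conclusion.** The allowance is an arithmetic error: it should be 78 (388 cases), so 66 is 12 too few. The 400-case total survives it, with 320 analysable cases and about 0.91 power at 8%, provided that carriers are no more common among cases than in the population and failures stay within about 3%.

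If the variant has the HR of 2 assumed for its own test, 298 to 267 cases remain before any failures, and power at 8% is about 0.89 to 0.85 at two controls per case. These figures rest on Table 1 being right, on interpolation between two of its entries, and on the HR of 2 applying to carriers overall. Even the lowest count, 267, exceeds the 230 that the table requires for 0.8 power, and the main 12% assumption is not threatened. The point calls for a correction to the text, not for a redesign.

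**What to change.** In the paragraph on methylation among non-carriers:

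1. Replace 66 by 78, giving 388 cases.
2. State that 400 cases leave about 3% for analytical failure, and give the failure rate expected from the assay.
3. Say that the carrier share among cases will exceed the population share if the variant raises risk. Restate power at 8% methylation as about 0.91 with no variant effect and about 0.85 to 0.89 with a variant HR of 2 (two controls per case, before failures), and above 0.9 at 12–13%.

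The cost is a few sentences. Enrolment stays at 400 cases and 800 controls, and no analysis changes.

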### **Statistical analysis of data.**

The potential association between methylation and risk of cancer will be performed by Cox multivariate analysis as the primary analysis. In addition, for sensitivity analysis we will perform logistic regression analysis. In both analyses, potential confounding variables will be included as co-variables, similar to our WHI AS543 study now in revised review in JAMA Oncology. The co-variables included will include age, race, previous hormone usage, DNA extraction method and geographical location. Methylation positivity for each sample will be determined based on presence fully methylated alleles (VEF), and the laboratory analysis conducted blinded to case control identity. Optimization of cutoff values will be performed using R package OptimalCutpoints (v1.1-4).(100).

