### Specific aims.

1. We will assess the HR for right-sided and left-sided colon cancer separately related to WBC *MGMT* methylation status using a case-control designed study
2. We will assess the HR for glioblastoma multiforme related to WBC *MGMT* methylation status using a case-control designed study
3. We will assess the HR for high-grade diffuse B-cell lymphomas related to WBC *MGMT* methylation status using a case-control designed study

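### The primary Cox model is named without matched-set strata or inclusion weights; fitted as described to the matched nested case-control sample, it shrinks a true HR of 2 to about 1.5-1.85

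*Protocol*

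**What the plan says.** Under Power analysis determining number of participants, the protocol fixes the design: cases are compared with "matched controls drawn from the WHI biobank in a nested case-control design". The planned sizes are 400 cases and 800 controls (1:2) for each of right-sided colon cancer, left-sided colon cancer and lymphoma, and 195 cases and 780 controls (1:4) for glioblastoma.

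The target is a hazard ratio. The glioblastoma aim, for example, reads "We will assess the HR for glioblastoma multiforme related to WBC *MGMT* methylation status using a case-control designed study", and the other two aims are built the same way. The planning value for the colon tests is "For both tests, we assume a HR of at least 2".

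Under Statistical analysis of data, the primary model is given as "The potential association between methylation and risk of cancer will be performed by Cox multivariate analysis as the primary analysis", followed by "In addition, for sensitivity analysis we will perform logistic regression analysis". Both models take the same adjustment: "The co-variables included will include age, race, previous hormone usage, DNA extraction method and geographical location". The section refers to an earlier WHI study (AS543) for the choice of confounders. It does not mention the matched sets, sampling probabilities, a robust variance, the time axis, or when a control's follow-up ends. The matching factors are not named anywhere in the protocol.

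**The concern.** In a nested case-control sample the proportion of cases is set by the matching ratio, not by incidence. Cases are one third of the sample at 1:2 and one fifth at 1:4. A Cox model recovers the cohort HR from such a sample if each case is compared only with its own sampled risk set, or if controls are weighted up to the cohort they represent. Without either, every risk set is over-filled with people who later become cases. These carry the exposure more often, so the contrast between a case and its comparators is diluted.

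The stake is the number the aims promise. The primary HR would be pulled toward 1 by an amount that depends on the matching ratio, so the same true effect would look somewhat larger in glioblastoma than in colon cancer or lymphoma. The protocol wants to view these three cancers together. The logistic sensitivity analysis would also disagree with the primary result for purely technical reasons.

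**Working it through.** **Inputs from the protocol.** True HR 2; methylation frequency in controls 12% (8% and 15% also used in its Table 1); 400 cases at 1:2 or 195 cases at 1:4; cohort of 160,000; about three decades of follow-up.

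**Assumed, because the protocol gives no figure.** Incidence-density sampling matched on year of age; age effect 0.04 per year on the log hazard; three censoring patterns (uniform 20-28 years; exponential attrition with an 18-28 year cap; uniform 3-25 years).

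**The plan's own figures.** The protocol gives no figure for what its Cox model would estimate. Its glioblastoma power statement (0.9) reproduces: 195 cases, 1:4, OR 2 gives 0.897 at 12% and 0.936 at 15%. The 195 cases in Table 1 (HR 2, 12%, 1:2, power 0.9) do not reproduce: a two-sided two-proportion formula gives 241. Nothing below depends on that entry.

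**Closed form at 12%.** Exposure among cases is 2 × 0.12 / (1 + 0.12) = 0.2143.

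*Controls keep their own follow-up.* The unweighted model treats the sample as a cohort, so its HR is about ln(1 − F1) / ln(1 − F0), where F1 and F0 are the case fractions among exposed and unexposed.
- 1:2: F1 = 0.2143 / (0.2143 + 2 × 0.12) = 0.472; F0 = 0.7857 / (0.7857 + 2 × 0.88) = 0.309. HR = ln(0.528) / ln(0.691) = 1.73.
- 1:4: F1 = 0.2143 / (0.2143 + 4 × 0.12) = 0.309; F0 = 0.7857 / (0.7857 + 4 × 0.88) = 0.182. HR = 1.83.

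*Controls stopped at the case's index date.* The HR is about the exposure odds of cases divided by those of the mixed case-plus-control risk set.
- Case odds: 0.2143 / 0.7857 = 0.273.
- 1:2: mixed odds 0.4543 / 2.5457 = 0.178. HR = 1.53.
- 1:4: mixed odds 0.6943 / 4.3057 = 0.161. HR = 1.69.

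**Simulation.** 250 cohorts per scenario, true HR 2:

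| Analysis | 1:2 | 1:4 |
|---|---|---|
| Cox, no strata or weights, own follow-up | 1.66-1.73 | 1.79-1.85 |
| Cox, no strata or weights, index-date end | 1.52-1.56 | 1.66-1.73 |

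Over both ratios, Cox stratified on matched set (conditional logistic), unconditional logistic and weighted Cox all return about 1.96-2.05.

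**Coverage of HR 2 by the nominal 95% interval.** At 1:2 it is 70-83% with own follow-up and 36-58% with index-date end, against 94-97% for conditional logistic. At 1:4 the loss is milder: about 90-96% and 83-90% at methylation frequencies of 12% and 15%.

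**Under HR 1** (800 cohorts for each of two designs). The unstratified, unweighted Cox averages 0.99-1.00 and rejects 3.5-6.5% of the time. The Monte Carlo standard error is √(0.05 × 0.95 / 800) = 0.8 points, so this is compatible with 5%.

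**Power** (12%, 400 cases, 1:2). It is 0.98 with own follow-up, as for conditional logistic, and 0.92 with index-date end.

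**Weighted Cox needs a robust variance.** With its model-based standard error it rejected a true null 12.4% of the time at 1:2 and 9.2% at 1:4.

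**The case against.** The strongest reply is that the protocol never says unstratified or unweighted. A set-stratified or weighted Cox model is also a multivariable Cox analysis and fits the sentence. An SAP may exist that settles strata, weights and time axis, and the reference to AS543 may imply a method not visible here. The authors plainly know that the design is nested and matched.

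Part of this stands. A reader might infer that the protocol has chosen an ordinary Cox model and decided to ignore the matching. The text does not support that; it is silent. But it does not leave the model open either. It names the primary model, the sensitivity model and the covariates entering both, and omits the element that makes Cox valid in this design. Entering age and race as ordinary covariates reads most naturally as an unstratified fit.

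Three further inferences go too far:
- *That false positives are inflated.* The null simulations show the level is kept, and the bias is toward 1.
- *That the logistic analysis is spoiled too.* Unconditional logistic regression with age as a covariate returned about 2. This was shown for matching on age only; the real matching factors are not stated.
- *That the intervals generally miss the truth, or that the two ratios give wholly incomparable results.* Coverage at 1:4 is near nominal with own follow-up, and the closed-form gap between ratios is 1.73 against 1.83, or 1.53 against 1.69. It is a real artefact of modest size.

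**Conclusion.** The point holds as a defect in how the primary analysis is specified. Fitted with only what the section lists, the Cox model does not estimate the cohort HR of the aims. At a true HR of 2 it gives about 1.5-1.75 at 1:2 and 1.65-1.85 at 1:4, and at 1:2 the nominal 95% interval covers the truth about 36-83% of the time. The spread comes mainly from the unstated end of controls' follow-up. The harm is to the size and interval of the primary HR and to comparisons across cohorts, with some loss of power if controls are stopped at the index date.

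The direction of the bias follows from the design and is confirmed by closed form. The exact figures rest on the assumed sampling, age effect and censoring patterns. The conclusion is conditional on the model being fitted without strata or weights, which the protocol neither states nor rules out.

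**What to change.** In Statistical analysis of data, state one of the following as primary:
- a Cox partial likelihood stratified on matched set (equivalent to conditional logistic regression), adjusted for those listed covariates that are not matching factors; or
- an inclusion-probability-weighted Cox model with robust variance, which also accommodates the planned sharing of controls across cancers.

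Name the matching factors, the time axis and the end of follow-up for controls. Do not use an unweighted, unstratified Cox model as primary. The logistic sensitivity analysis can stay.

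The cost is a few sentences and no new samples or assays. The protocol does not say that matched-set identifiers or sampling probabilities will be kept with the data. They must be requested at control selection, and reuse of a control in more than one comparison must be recorded.

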located within a thousand base pairs upstream of the gene, are typically characterized by a high density of CpG dinucleotides into so-called CpG islands (6). Epigenetic regulation involves at least two different processes, CpG methylation, and histone demethylations (7). These two events in general appear in concert (8), making CpG methylation a suitable marker of epigenetic silencing of many genes. Abnormal epigenetic regulation is coined epimutations and may occur *in utero*, so-called **constitutional epimutations**, or in different tissues later in life as **somatic epimutations**. The fact that epigenetic regulation is influenced by genetic but also environmental factors including pollutants (9-14) makes **epimutations** strong candidates linking environmental agents to cancer risk.

**Constitutional epimutations** presents epigenetic disturbances arising *in utero*, normally affecting tissues belonging to all three germ layers (15, 16). **Constitutional methylations** are classified into two major groups; **primary epimutations** where no associated DNA sequence variant is detected, and **secondary epimutations**, occurring as a consequence of a local *cis*-acting DNA alteration (17, 18). While gene silencing through somatic epimutations are frequently observed in cancer tissue (19), despite some preliminary reports (evidence summarized in (20)), very few studies have investigated constitutional epimutations as potential underlying causes in carcinogenesis. Carcinogenesis evolve over time, including early life events (21) and for certain cancer forms, indirect evidence points toward prenatal events to be of importance for later carcinogenesis (22).

While secondary constitutional epimutations in tumor suppressor genes like *MLH1*, *BRCA1* and *MSH2* (11, 23-26) have been associated with elevated cancer risk, such secondary epimutations are extremely rare (20). Notably, secondary epimutations in general are easily detected due to the fact that they typically affect approximately 50% of the alleles. In contrast, while primary epimutations seems to occur more frequently, they may easily be overlooked due to a low-mosaic expression (27).

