## **Current study.**

**Here, we will confirm constitutional primary epimutations of *MGMT* to be a cancer risk factor by evaluating WBC *MGMT* methylation as risk factor for colorectal cancer, glioblastomas and high-grade lymphomas.** Data generated will be used also to model the mechanism(s) of CpG methylation building up across the promotor area, evaluating the different models outlined in Figure 1.

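### The primary Cox model is not tied to the non-carrier set and does not adjust for rs16906252, and the total-group glioblastoma test mixes primary and secondary epimutations

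*Protocol*

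**What the plan says.** The Current study section of the protocol sets the goal: "we will confirm constitutional primary epimutations of *MGMT* to be a cancer risk factor". The Background defines a primary epimutation as one "where no associated DNA sequence variant is detected".

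The section on power analysis deals with rs16906252 directly. For colon cancer, the methylation effect is to be tested after "Removing all carriers of the SNP rs16906252 variant allele", and the 400/800 cohort size allows for that loss. A second test looks at the SNP among unmethylated women, and both tests assume an HR of at least 2. Lymphoma is sized on a calculation like the one for colon. For glioblastoma (195 cases, 1:4 controls), "promoter methylation may be tested in the total group with a power of 0.9"; the same sentence puts methylation and the SNP tested separately at a power between 0.8 and 0.9.

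The section on statistical analysis says that the association between methylation and cancer "will be performed by Cox multivariate analysis as the primary analysis", with logistic regression as the sensitivity analysis. Of the adjustment set it says: "The co-variables included will include age, race, previous hormone usage, DNA extraction method and geographical location". It does not mention rs16906252, either as a covariate or as a restriction on who is analysed.

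**The concern.** The only section that names a primary analysis does not refer to the genotype-restricted test that matches the objective. The Specific aims speak of methylation status with no genotype limit. Read literally, the primary Cox model therefore runs in all women with no account of the SNP, as does the glioblastoma test that carries the 0.9.

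This matters because the variant is linked to methylation and the plan treats it as a possible risk factor in its own right. If it raises risk by a route other than methylation, an unadjusted all-women analysis credits part of that effect to methylation. Even without such a route, the all-women estimate blends epimutations that accompany a DNA variant with those that do not, so it does not isolate what the Current study section claims. Two methylation HRs could then be reported as primary, with nothing in the protocol to say which one governs.

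**Working it through.** **Inputs (protocol, power section).** 575 women: 35 methylated carriers, 49 unmethylated carriers, 65 methylated reference homozygotes, 426 unmethylated reference homozygotes. Glioblastoma 195/780; other cohorts 400/800. Planning effect 2 for both methylation and SNP; alpha 0.05.

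**Assumptions.** Two-sided testing; this table holds for WHI controls; odds ratios stand in for HRs; matching is ignored.

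**1. The plan's own power.** Two-proportion formula, 195 cases, 1:4, OR 2:
- All women: 0.897 at 12% methylation and 0.936 at 15%. The stated 0.9 is reproduced.
- Methylation in non-carriers: with 167 cases (85.4% of 195), 0.852–0.899; with 156 cases (20% carriers), 0.829–0.880. Both lie within the stated 0.8–0.9.

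**2. SNP–methylation link.** Methylated: 35/84 = 41.7% of carriers and 65/491 = 13.2% of non-carriers. OR = (35 × 426)/(49 × 65) = 4.68. Carriers are 35/100 = 35% of methylated women and 49/475 = 10.3% of unmethylated women. The protocol writes "A modest correlation between the rs16906252 and promoter methylation has been reported previously", which describes earlier literature. In its own table the phi coefficient is 0.26, but the odds ratio is large enough to matter.

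**3. Spurious methylation OR.** With no methylation effect within genotype and a direct SNP odds ratio *s*, weight the carrier cells by *s* among cases:

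OR = [(35*s* + 65)/(49*s* + 426)] ÷ (100/475)

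- *s* = 1.5: (117.5/499.5)/0.2105 = 1.12
- *s* = 2: (135/524)/0.2105 = 1.22
- *s* = 3: (170/573)/0.2105 = 1.41

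Setting the OR to 2 and solving gives *s* of about 8.

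**4. Rejection at nominal 5%, unadjusted, all women** (normal approximation):

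| SNP OR | 195/780 | 400/800, if unrestricted |
|---|---|---|
| 1.5 | 0.09 | 0.11 |
| 2 | 0.18 | 0.26 |
| 3 | 0.43 | 0.62 |

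Worked cell for *s* = 2, 195/780: methylated proportion 135/659 = 0.205 in cases and 0.174 in controls; null SE 0.0308, alternative SE 0.0319. The upper tail is Φ[(0.0309 − 1.96 × 0.0308)/0.0319] = 0.179 and the lower tail 0.002, total 0.18.

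A simulation (2,000 runs, unmatched logistic regression, *s* = 2) gave 0.166 and 0.264. Adding carrier status gave 0.053 and 0.049. At 1.5 the unadjusted rates were about 8% and 11%.

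**5. Power under the remedies** (methylation OR 2, 575-woman table):
- Reference homozygotes only, glioblastoma: cases 195 × (130 + 426)/675 = 161, controls 780 × 491/575 = 666, methylated 13.2% in controls and 130/556 = 23.4% in cases. Power about 0.86. For 400/800, about 0.98.
- All women with carrier status in the model, glioblastoma: variance inflation 1/(1 − 0.265²) = 1.08; power about 0.95 with or without adjustment.

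**The case against.** The best defence is that the protocol already contains the right test. Under its own heading the power section removes carriers, which matches the definition of a primary epimutation, and it sizes the colon cohorts for the loss. Lymphoma follows that calculation, and glioblastoma has separate tests at 0.8–0.9. In non-carriers genotype is constant, so confounding by this SNP cannot arise. This stands. A reader might infer that the primary-epimutation objective goes unanswered; the documents do not support that.

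It is also fair that the protocol does not rank the two glioblastoma tests, that it allows primary and secondary epimutations to be assessed separately or together, and that the planning HR of 2 for the SNP is not evidence of a SNP effect. If the variant acts only through methylation, the association is real but secondary, not spurious. A reader might also infer that a positive result could be wholly due to the variant. That does not fit an effect of the planned size: a spurious odds ratio of 2 needs a SNP odds ratio of about 8. The 26% figure applies only if a 400/800 cohort is analysed unrestricted, which the power section does not describe.

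Analysis sets are often left to the SAP, which is not shown. Here, however, the protocol itself names the primary model and lists its covariates, without linking either to the non-carrier set. That gap remains.

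**Conclusion.** The concern holds in a limited form. The right test is planned, but the analysis named as primary is neither restricted to non-carriers nor adjusted for rs16906252, and an unadjusted total-group glioblastoma test stands beside the separate ones with no rule on which supports the claim. In an all-women analysis, a direct SNP odds ratio of 1.5 to 2 with null methylation gives a false methylation odds ratio of about 1.12 to 1.22. The type I error is then about 8–9% to 17–18% for glioblastoma, and about 11% to 26% for a 400/800 cohort if it is run unrestricted.

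These figures rest on the 575-woman table applying to WHI controls and on a SNP effect that bypasses methylation. The value 2 is the plan's own planning effect; 1.5 is assumed to show the range. With no direct SNP effect there is no type I inflation, but the total-group estimate still mixes the two kinds of epimutation.

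**What to change.** - In the section on statistical analysis, state that the primary methylation model in all four cohorts (right colon, left colon, glioblastoma, lymphoma) is run in rs16906252 reference homozygotes, the set that the power section describes.
- Add carrier status (any variant allele versus reference homozygote) as a covariate in any model run in all women, including the total-group glioblastoma test and any all-women logistic sensitivity analysis.
- Label every total-group HR as primary and secondary epimutations combined, and say that it does not by itself support the primary-epimutation claim. Adjustment alone is not enough: it removes the SNP's direct effect but still averages over carriers and non-carriers.

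The cost is small. The genotype is already needed for the planned SNP tests, so no new samples are required. The glioblastoma test of primary epimutations would carry the 0.8–0.9 already stated for separate testing (about 0.86 on the 575-woman table) instead of 0.9. Adjusting the total-group test costs almost no power.
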